### School-level outcomes

#### School grounds audit

The ‘Artificial Intelligence-based School Audit’ (AISA) online audit tool, recently developed by the research team, will be used to assess the school’s physical environment, to be assessed as a potential moderator of the intervention effects. The audit tool quantifies the dimension (m^2^) of the school footprint and the percentage of the school grounds taken up by buildings and on-site car parking, sports courts, green spaces (eg, trees, open green spaces), playgrounds and covered areas (eg, shade sails). AISA uses an advanced artificial intelligence methodology and deep learning segmentation pipeline to quickly and accurately label the above environmental features using date-stamped satellite images of school grounds. Some additional environmental characteristics not captured by AISA will be audited in person (eg, sports or playground equipment, playground/sports courts markings, playgrounds/outdoor spaces separated by a physical barrier, aesthetics of facilities, bicycle parking).

### Data analysis

Analysis of the primary and secondary outcomes will be performed using Stata 18 for Windows (StataCorp LP) and RStudio V.1.4.453 (R V.3.6.3; R Foundation for Statistical Computing, Vienna, Austria).

Descriptive analyses will be employed to depict the quantitative data collected for all variables of interest, including students’ demographic characteristics, physical activity, sedentary behaviour, sleep, well-being, class engagement, school environment and intervention implementation measures (eg, school audit data) at each time point. Data will be examined for missing values, outliers and distributional assumptions. Teachers’ demographic characteristics and survey responses from both intervention and control groups will be described.

For the primary outcomes, random intercept linear mixed models will be used (where the unit of the analysis (students) will be nested within year levels within schools) to examine the intervention effects on primary (physical activity and sedentary time) and secondary (sleep and well-being, class and school engagement, reducing sitting time, increasing light, moderate and vigorous physical activity, self-report physical activity/sedentary behaviours, observed physical activity during recess and lunch time and engagement with the intervention strategies) outcomes among adolescents. All models will be adjusted for measured confounders age, gender, baseline values, socioeducational advantage strata (high vs low ICSEA) and school type (Government, Independent, Catholic).

The programme’s reach, adoption, implementation, and organisational-level maintenance aspects will be presented descriptively. Linear or logistic regression models will be used to compare differences between intervention and control groups in teacher perceptions of school readiness, climate, and environment, as well as teacher practices, competence levels, and implementation barriers, adjusting for baseline values as covariates. The school grounds audit data will be analysed using descriptive statistics to characterise the physical environment of intervention and control schools and interactions with the intervention effects will be examined to determine if there was a potential moderator effect by school environment.

Qualitative data will be transcribed and thematically analysed using NVivo V.14. The coding and theme development process will initially follow a deductive approach, guided by the study aims and domains within the Proctor’s implementation outcomes framework.^34^ Subsequently, an inductive method will be employed, driven by the content of the data itself. Two independent researchers will be responsible for coding the data.

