**Methods and analysis:**

A type II hybrid implementation-effectiveness trial will be conducted using a mixed-methods design. For the implementation trial, *TransformUs Secondary* will be disseminated via key organisations nationally (eg, state departments of education) and available to all Australian secondary schools (n=1453). Implementation outcomes will be evaluated using the RE-AIM framework (reach, adoption, implementation and maintenance). Data will be collected at the school and teacher levels via the TransformUs website (website analytics), descriptive quantitative surveys, text messages to teachers and qualitative interviews with teachers, students and representatives from key organisations. Descriptive statistics will summarise quantitative data, with regression analyses examining the associations between implementation strategies and outcomes. Implementation levels will be classified as low, moderate or high based on the extent of intervention delivery. Qualitative data will be thematically analysed.

We will assess effectiveness outcomes in 10 Victorian secondary schools using a pragmatic 1:1 waitlist control design. The target sample is 600 Year 7–10 students (12–16 years). Primary outcomes include adolescents’ physical activity and sedentary time (assessed with accelerometry), and secondary outcomes include health (sleep and well-being), class and school engagement (on-task behaviour assessed via classroom observation and school attendance) and sitting time (assessed with posture monitors). Descriptive analyses will summarise students’ demographics, physical activity, sedentary behaviour and engagement, while mixed models will evaluate intervention effects on these outcomes, adjusted for confounders. Additionally, qualitative data will be thematically analysed using deductive and inductive coding in NVivo.

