#### Student attendance

Overall student attendance data will be collected for each participating school at baseline and 6 months. The percentage of actual full-time equivalent student days attended as a percentage of the total number of possible student days attended over the (reporting) period will be collected from the Australian Curriculum, Assessment and Reporting Authority website (https://www.acara.edu.au/contact-us/acara-data-access).

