#### Observed physical activity during recess and lunch

Students’ physical activity during recess and lunch will be assessed using the System for Observing Play and Leisure Activity in Youth (SOPLAY) at baseline and follow-up. SOPLAY is a validated tool for directly observing physical activity and associated environmental characteristics in free-play settings.^48^ SOPLAY provides objective data on the number of participants and their physical activity levels during play and leisure opportunities in targeted areas. The research staff will define the target areas. Separate scans are made for males and females, and simultaneous entries for contextual characteristics of areas including their accessibility, usability, and whether supervision, organised activities and equipment are provided. A map of the zones and SOPLAY data collection sheets will be provided to each research assistant. Observations will begin 5 min into recess and 10 min into lunch and occur every 5 min. Research assistants will rotate clockwise around the zones, with each group starting in a different zone. Observations will end 5 min before the end of recess/lunch. All observations will be recorded on the SOPLAY data collection sheet. The predominant type of activity engaged in by area users will also be recorded (eg, basketball, dance) (online supplemental file 4G).

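### The student-level mixed model is assigned to SOPLAY observations and, through 'school engagement', to attendance, but neither is collected at student level

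*Protocol article*

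**What the plan says.** The Data analysis section of the effectiveness trial specifies random intercept linear mixed models "where the unit of the analysis (students) will be nested within year levels within schools". The same sentence then lists the outcomes. The secondary list begins "secondary (sleep and well-being, class and school engagement, reducing sitting time" and ends with "observed physical activity during recess and lunch time and engagement with the intervention strategies". The next sentence fixes the covariates: "All models will be adjusted for measured confounders age, gender, baseline values", followed by ICSEA stratum and school type. The section's other regressions compare teacher survey outcomes or examine moderation by the school environment. No separate model is given for observed play or for attendance.

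On how the two outcomes are collected:

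- Observed physical activity during recess and lunch: "SOPLAY provides objective data on the number of participants and their physical activity levels during play and leisure opportunities in targeted areas". Also, "Separate scans are made for males and females". Scans are repeated every 5 minutes while research assistants rotate through zones.
- Student attendance: "Overall student attendance data will be collected for each participating school at baseline and 6 months". The figure is a percentage of possible student days, taken from an external authority.
- Abstract, Methods and analysis, on what engagement means: "class and school engagement (on-task behaviour assessed via classroom observation and school attendance".

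Both measures are placed under Student-level outcomes, although the article has a separate School-level outcomes heading.

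**The concern.** A model with the student as unit needs one row per student, with that student's school, year level, age, gender and baseline value. SOPLAY as described produces counts of whoever is in an area at the moment of the scan. Attendance as described produces one number for the whole school. If neither source can supply the rows or covariates, two secondary outcomes have no usable planned analysis. The unit, the summary measure and the model would then have to be chosen later, in a trial where schools and teachers know their allocation.

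**Working it through.** **1. The plan's own figure.** The only power statement in the article is for accelerometer MVPA: SD 17 min/day, difference 7 min/day, ICC 0.03, 80% power, alpha 0.05 (taken as two-sided), and 12 students analysed in each of 4 year levels, so 48 per school.

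- Unclustered requirement: 93 students per arm.
- Design effect: 1 + (48 − 1) × 0.03 = 2.41.
- Schools per arm: 93 × 2.41 / 48 = 224.1 / 48 = 4.67, rounded up to 5.
- Total: 10 schools × 60 recruited = 600 students, as stated.

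The figure reproduces. It rests on 480 student-level measurements (10 × 48) and says nothing about SOPLAY or attendance.

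**2. What the model needs against what is collected.**

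| Model term | SOPLAY | Attendance |
|---|---|---|
| Student as unit | no; headcount per area and scan | no; one value per school |
| Year level within school | not recorded | not available |
| Age | not recorded | not available |
| Gender | yes, scans are separate by sex | not described |
| Student's own baseline | no; school or area baseline only | no; school baseline only |
| ICSEA stratum, school type | yes, at school level | yes, at school level |

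SOPLAY has a further difficulty. With scans every 5 minutes, the same student may contribute to several counts, so the counts are not distinct students. The article gives neither the number of areas nor the number of scans per school, so no SOPLAY sample size can be calculated. The highest independent unit is the school, of which there are 10.

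**3. What attendance can support at the level collected.** There are 10 values per time point (5 v 5), or 20 over the two time points.

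- Unadjusted comparison: df = 10 − 2 = 8. Detectable difference at 80% power, two-sided 5% = (2.306 + 0.889) × SD × √(2/5) = 2.02 SD.
- With arm, baseline, ICSEA and school type (two terms): df = 10 − (1 + 1 + 1 + 1 + 2) = 4. Detectable difference 2.38 SD by the noncentral t, assuming the covariates explain no variance.
- For comparison, 480 independent students would give (1.960 + 0.842) × √(2/240) = 0.26 SD.

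The article gives no between-school SD for change in attendance. Assuming 1, 2 or 3 percentage points, the unadjusted detectable difference is 2.0, 4.0 or 6.1 percentage points.

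**The case against.** Five points can be made on the other side.

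- **The model sentence opens by referring to the primary outcomes.** It goes on to list the secondary outcomes, and the covariate sentence covers all models. This does not rescue the text.
- **Recess and lunch activity is also derived from the accelerometer, which is student-level.** True, but the listed item is observed activity, which matches the SOPLAY section heading, and light, moderate and vigorous activity is listed separately.
- **Attendance is not named in the Data analysis section, nor among the secondary outcomes under Measures.** This stands in part. The link runs through the abstract's definition of engagement, and the classroom engagement survey is another possible reading. The attendance limb is therefore less direct than the SOPLAY limb.
- **Outcome-specific models belong in an analysis plan.** An omission would be excusable. Here the article states a unit and covariates that the data cannot supply.
- **The planned school random intercept protects the arm comparison.** This stands against a stronger reading. A reader might infer that precision would be badly overstated, or that type I error would be severe. Copying each school's percentage to 48 students and ignoring clustering does give a simulated type I error of about 80%, but the plan does not ignore clustering. Inflated precision is not shown.

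A reader might also infer that the attendance reporting period misses the trial's visits. The article says that data are collected at baseline and 6 months and does not give the length or timing of the period, so a mismatch is not shown.

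**Conclusion.** The point holds. For SOPLAY it holds on the text alone: the outcome is assigned by name to a model needing student identity, year level, age and individual baseline, and the described method records none of these. For attendance it holds through the abstract's definition of school engagement: one percentage per school per time point cannot enter a student-level model.

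The scope is limited to secondary outcomes. Nothing here touches the accelerometer outcomes, the student surveys or the sample size. The detectable difference of about 2.0 between-school SDs (2.38 with the full covariate set) assumes 5 v 5 schools, equal variances and no variance explained by covariates. It reflects having 10 schools, and re-specifying the analysis does not improve it. The percentage-point figures rest on assumed SDs.

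**What to change.** Remove both outcomes from the student-level model and state the unit for each.

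- **SOPLAY:** summarise to the school, for example as the proportion of observed students who are active, by period (recess, lunch) and sex. Compare arms with the school as the unit, adjusted for the school's own baseline value. If scan- or area-level data are modelled instead, include a school random effect and allow for overdispersion or repeat counting; a plain binomial model with school and area effects would still treat repeat counts of one student as separate trials.
- **Attendance:** report each school's percentage and its change by arm, labelled descriptive. Say explicitly whether attendance is what school engagement means in the analysis section. Do not attach a permutation interval. Schools are assigned by availability and timing, so there is no randomisation to justify it. If the paired starts were respected as five pairs, there would be 2⁵ = 32 assignments and a smallest two-sided p of 2/32 = 0.0625.

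The change is to wording only and uses data already planned. The cost is that attendance carries no formal test and SOPLAY inference rests openly on 10 schools.

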### Data analysis

All statistical analyses will be performed using STATA 18 for Windows (StataCorp LP). Descriptive statistics will be used to summarise quantitative data collected from surveys (eg, teachers’ self-reported sociodemographic information, physical activity levels, perceptions of school readiness, climate and environment, as well as teacher practices, competence levels and perceived implementation barriers). The survey data regarding programme Reach, Adoption, Implementation and Maintenance will be also presented descriptively.

Similar descriptive statistics will be used to summarise the data for intervention implementation, including frequency, duration and confidence levels for incorporating active lessons, breaks and homework, as well as a commitment to continue implementing these strategies. Additionally, analyses will be conducted to examine associations between implementation strategies and outcomes, using regression analysis.

Linear or logistic regression models will be used to examine associations between various factors (such as teachers’ sociodemographic characteristics, physical activity levels, perceptions of school climate, etc) and implementation level, adjusting for multiple comparisons. The implementation levels will be determined using methods from a prior evaluation of the *TransformUs* efficacy trial.^35^ In brief, teachers will be categorised based on the extent of implementation, determined by the proportion of the entire intervention delivered, considering both dose-delivered and fidelity. The implementation levels will be classified as: (1) ‘low’ (<33% of the entire intervention delivered); (2) ‘moderate’ (33%–67% delivered) and (3) ‘high’ (>67% delivered).

Qualitative data will be transcribed and thematically analysed using NVivo V.14. The coding and theme development process will initially follow a deductive approach, guided by the study aims and domains within Proctor’s implementation outcomes framework.^34^ Subsequently, an inductive method will be employed, driven by the content of the data itself. Two independent researchers will be responsible for coding the data.

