### Effectiveness trial

The effectiveness trial will employ a pragmatic waitlist control design. Secondary schools will be assigned (based on the school availability and timing requirements) to the *TransformUs Secondary* intervention (n=5 schools) or a waitlist control ‘usual practice’ condition (n=5 schools). Waitlist control schools will receive the intervention after 6 months (approximately 2–3 school terms).

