### Sample size and power calculations

Students will be recruited from 4-year-levels (Years 7, 8, 9 and 10) from each of the 10 schools. It is estimated an average of 15 students will be recruited per year level, enabling at least 12 for analysis, assuming up to 20% dropout. We will conservatively apply a design effect based on an intraclass correlation coefficient (ICC) of 0.03. Assuming an SD for the MVPA outcome of 17 min/day (Corder *et al* 2020), we will have 80% power to detect a minimum difference between groups of 7 min/day MVPA, for α=0.05. Therefore, participants in the effectiveness trial will include one nominated school leader per school (n=up to 10); approximately eight Year 7–10 teachers per school (n=up to 80) and all Year 7–10 secondary students attending classes with the consenting teachers (only consenting student will take part in the evaluation). The recruitment target will be approximately 600 students in total (approximately n=60 students per school). Sample size calculations were conducted in Stata/SE 16 using the power two means command.

Including an effectiveness trial that is accessible to all schools in Victoria enhances the generalisability of the results by incorporating diverse student populations representing various educational contexts, needs and resources. This broad approach improves the reliability of findings, reflecting how the intervention performs across different demographics and settings, making the results more applicable to other schools in the state. However, using a subsample may limit generalisation as it may not fully represent the student population’s diversity. Smaller or more localised samples could be influenced by specific local conditions, reducing the ability to make broader conclusions. While subsamples offer valuable insights, they may lack the comprehensiveness needed for strong generalisations, which we have acknowledged as a limitation.

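### The between-arm teacher comparisons in the effectiveness trial name no term for school, although whole schools are allocated, so standard errors are too small if teachers within a school resemble each other

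*Protocol article*

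**What the plan says.** The unit of allocation is the school. Under Effectiveness trial the article states: "Secondary schools will be assigned (based on the school availability and timing requirements) to the" intervention or the waitlist, with five schools in each. The section Sample size and power calculations expects "approximately eight Year 7–10 teachers per school (n=up to 80" in total).

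The Data analysis section of the effectiveness trial then describes two kinds of model:

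- **Student outcomes:** random-intercept linear mixed models, "where the unit of the analysis (students) will be nested within year levels within schools".
- **Teacher outcomes** (perceptions of readiness, climate and environment; practices; competence; barriers): "Linear or logistic regression models will be used to compare differences between intervention and control groups in teacher perceptions of school readiness" and the other listed measures, "adjusting for baseline values as covariates". No random effect, clustered variance or school-level analysis is mentioned.

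The Data analysis section of the implementation trial uses similar wording for the correlates of implementation level: "Linear or logistic regression models will be used to examine associations between various factors". Nothing is allocated there, but several teachers from one school may register.

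**The concern.** When whole schools are allocated, the information about the arm effect lies mainly between schools. A regression with one row per teacher and no allowance for school treats up to 80 teachers as 80 independent units. In fact they come from ten allocated units.

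A positive correlation is plausible here. Several outcomes are ratings of something all teachers in a school share: its readiness, climate, environment and policies. Intervention teachers in one school also share a training session and a school implementation fund, so responses at follow-up may stay correlated after baseline adjustment. The case is weaker for personal measures such as a teacher's own competence or perceived barriers.

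At stake are claims that the programme changed school climate or teacher practice. In a hybrid design with implementation outcomes at school and teacher level, such claims may carry weight in decisions about scale-up.

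**Working it through.** **1. The article's own clustered calculation (students).** Inputs from Sample size and power calculations: difference 7 min/day, SD 17 min/day, power 80%, alpha 0.05 (two-sided assumed), 12 analysed in each of 4 year levels = 48 per school, and a "design effect based on an intraclass correlation coefficient (ICC) of 0.03".

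- Individually: n = 2 × (1.960 + 0.842)² × 17² / 7² = 92.6, so 93 per arm.
- Design effect = 1 + (48 − 1) × 0.03 = 2.41.
- 93 × 2.41 = 224 per arm; 224 / 48 = 4.67, so 5 schools per arm.
- 10 schools × 60 recruited = 600 students.

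The stated numbers reproduce. The article therefore already treats school as a source of correlation for students. It gives no sample size, power or ICC for teacher outcomes.

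**2. The teacher comparison as written.** Inputs: 5 v 5 schools and m = 8 teachers per school (80 in total). The ICC is an assumption, to be read as the correlation remaining after baseline adjustment. The calculation assumes no arm effect and no systematic difference between the schools in the two arms.

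- Design effect: DE = 1 + (m − 1) × ICC.
- True standard error / naive standard error ≈ √DE.
- True size of a nominal 5% test ≈ 2 × [1 − Φ(1.96 / √DE)].

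Example at ICC 0.03: DE = 1 + 7 × 0.03 = 1.21, √DE = 1.10, 1.96 / 1.10 = 1.782, size = 7.5%.

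| Residual ICC | DE | √DE | Effective n of 80 | True size (formula) | True size (simulated) | Test on school means, 8 df (simulated) |
|---|---|---|---|---|---|---|
| 0.03 | 1.21 | 1.10 | 66 | 7.5% | 7.6% | 5.1% |
| 0.05 | 1.35 | 1.16 | 59 | 9.2% | 9.3% | 5.1% |
| 0.10 | 1.70 | 1.30 | 47 | 13.3% | 13.5% | 5.2% |
| 0.20 | 2.40 | 1.55 | 33 | 20.6% | 21.1% | 5.1% |

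The simulation used 40,000 runs of 5 v 5 schools. It compared an ordinary two-sample t-test on teachers with a t-test on the ten school means.

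**3. Fewer respondents.** Eight per school corresponds to the stated maximum of 80. With 4 per school, DE = 1 + 3 × ICC and the size is 6.1% (DE 1.09), 8.6% (DE 1.30) and 12.1% (DE 1.60) at ICCs of 0.03, 0.10 and 0.20. Simulation gave 6.1%, 8.6% and 12.4%.

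**4. Implementation trial.** For an association with a teacher-level covariate, the variance inflation is roughly 1 + (m − 1) × ICC(covariate) × ICC(outcome). If the covariate is not correlated within schools, its ICC is 0 and the factor is 1, so there is no inflation. If it is shared by the whole school, its ICC is 1 and the factor becomes the usual design effect. The article does not say how many teachers per school will take part, so m is unknown and no figure can be given.

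**The case against.** The strongest defence has four parts.

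- **The article is condensed.** A linear or logistic regression with school-clustered standard errors would still fit the wording, and the variance estimator could sit in an analysis plan that is not shown. This stands in part: nothing rules out a clustered variance. But the article does state a method and an adjustment for teachers, and both differ from the nested model it has just given for students. A reader would implement a model without school. The sentence that adjusts all models for confounders does not help: it belongs to the student paragraph and lists fixed covariates, which leave residual between-school variance in place.
- **The outcomes are not headline outcomes.** This stands. The listed primary and secondary outcomes are student outcomes, and the sample size does not rest on teachers.
- **The true ICC may be small.** This stands as a limit on size. The only ICC in the article is 0.03, for student activity. Baseline adjustment will absorb part of any stable difference between schools, and fewer than eight teachers may respond. At 0.03 the inflation is modest.
- **The implementation trial is different.** This also stands. A reader might infer that every association with implementation level there has too small a p-value. The article does not support that: several factors, such as a teacher's age or own physical activity, may vary largely within schools, and for those there is little or no inflation.

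**Conclusion.** The point holds for the between-arm teacher comparisons in the effectiveness trial. As written, they allow for no correlation within the allocated unit, and their standard errors are too small whenever the residual within-school ICC is positive. With eight teachers per school the true size of a nominal 5% test is about 7.5% at ICC 0.03 and about 9%, 13% and 21% at 0.05, 0.10 and 0.20. These ICCs are assumptions, because the article gives none for teachers; 0.03 is borrowed from student activity. The concern is strongest for ratings of the shared school.

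A reader might go further and infer that the trial's main effectiveness conclusions are at risk. They are not at risk from this: the student models carry nested random intercepts. The point is therefore one that should be fixed, not one on which the trial's main result depends.

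For the implementation trial the point is narrower. It concerns determinants shared within a school, such as climate, and its size cannot be stated.

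**What to change.** **Effectiveness trial, teacher outcomes.**

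- Continuous outcomes: a linear mixed model with arm, baseline value and a random intercept for school, using Kenward-Roger or Satterthwaite degrees of freedom.
- Binary outcomes, or as one method for all: reduce each school to one baseline-adjusted summary and compare the ten summaries on a t distribution with about 8 degrees of freedom. The two small-sample corrections above do not carry over directly to logistic mixed models.
- Do not rely on uncorrected cluster-robust standard errors with only ten schools.

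**Implementation trial.** Add a school random intercept, or standard errors clustered by school. Clustered standard errors are more reasonable there if the expected number of schools (about 70 registering, with a smaller share consenting to research) yields enough clusters.

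**Cost.** One sentence in each analysis section and no new data. Confidence intervals widen. For the comparison of ten school summaries the factor is about √DE × t(8 df) / t(78 df), with t values 2.306 and 1.991: 1.10 × 1.158 = 1.27 at ICC 0.03, and 1.30 × 1.158 = 1.51 at ICC 0.10. Some teacher comparisons will be imprecise, which reflects having ten allocated schools.
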